### 60- and 90-Day Medication-Related Hospital Readmissions

*ICD-10-AM* “Y” codes to determine “drugs, medicaments and biological substances causing adverse effects in therapeutic use” will be used to identify 60- and 90-day medication-related hospital readmissions.

### Patient Experience Survey

A patient survey will be developed and administered at the end of the trial to assess patient experience and elicit patient preferences using a discrete choice experiment (DCE). Patient experience will be assessed with a series of multiple-choice, short-answer, and Likert scale questions. Adjustments will be made to the survey after piloting, and the final survey will be uploaded into Qualtrics. The DCE will be conducted to determine the relative importance of each element of the intervention to the patient population and the associated willingness to pay. DCEs use random utility theory to estimate the value of health service provision based on individual attributes of the service [39]. They involve asking the consumers to make discrete choices between mutually exclusive options containing different levels of predefined attributes. The survey will be administered to all patients in the trial where possible.

### Economic Evaluation

Cost-effectiveness of the pharmacist-led interdisciplinary TOC service, compared to usual care, for patients post-AMI and/or CS will be determined using data from the primary analysis. A cost-effectiveness analysis will be undertaken to determine the net cost of providing the intervention and any difference in the cost of unplanned 30-day readmissions (primary outcome) compared with the usual care group. Costs will be quantified using data from the trial, the local hospital business unit, and expert opinion. Effectiveness will be measured as the incremental reduction in unplanned 30-day readmissions, and this will be used to determine the incremental cost-effectiveness ratio. All costs will be defined from the perspective of the state health system for a single year (the financial year of the trial) and currency (Australian dollars, AUD). *P* values less than .05 will be considered statistically significant. The analysis method may be adapted to a cost-minimization analysis or cost-consequence analysis, if required, once the primary outcomes have been analyzed. Sensitivity analysis will be conducted to assess the level of confidence in the conclusions of the economic evaluation. Sensitivity analysis is expected to include variations in resource costs, hospitalization costs, remuneration and savings from the program, and outcome measures, but specific attributes will be identified and their variation limits will be determined after the primary cost-effectiveness analysis has been completed.

The implementation and maintenance secondary outcomes will be evaluated using quarterly interviews with the TOC team to identify site-specific adaptations as well as enablers and barriers to TOC delivery.

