#### Secondary Objective

The secondary objective is to evaluate the impact of the TOC service based on key domains of the RE-AIM (Reach, Effectiveness, Adoption, Implementation, and Maintenance) framework [20], including the following:

Reach: The target population by the absolute number, proportion, and representativeness of patients who are willing to participate in the RECARD TOC service.Proportion of patients who engage with the TOC service: The proportion of patients who consent to and engage with the TOC service, compared with the broader population of patients with AMI/CS and the high-risk patients across the sites (Princess Alexandra Hospital [PAH], Royal Brisbane and Women's Hospital [RBWH], and Townsville University Hospital [TUH]).Effectiveness: The impact of the TOC service on secondary outcomes, including clinical effects, potential negative effects, and economic outcomes.30-day all-cause readmissions: All patients who are readmitted to the hospital for any presentation or reason within 30 days.60-day all-cause readmissions: All patients who are readmitted to the hospital for any presentation or reason within 60 days.90-day all-cause readmissions: All patients who are readmitted to the hospital for any presentation or reason within 90 days.Subanalysis of the primary outcome by cohort: 30-day medication-related readmission subanalysis for post-AMI patients and CS patients as subgroups.Subanalysis of the primary outcome by site: 30-day medication-related readmission for metropolitan versus regional sites.Subanalysis of the primary outcome by intervention: 30-day medication-related readmission for high-risk patients who received the intervention (TOC service) and those who did not, as subgroups.Preventable harm: Preventability of 30-day medication-related readmissions as assessed through the modified Schumock and Thornton criteria [21].Severity of harm: Severity of 30-day medication-related readmissions as defined through severity definitions by Morimoto et al [22].Patient experience: Patient experience and preferences assessed through a survey.Cost-effectiveness: Economic evaluation to assess the cost per readmission avoided.Adoption: The target staff, settings, systems, and communities by the absolute number, proportion, and representativeness of settings and staff willing to initiate and deliver the TOC service.TOC staff field notes during service delivery: TOC service staff (ie, TOC pharmacist, TOC nurse, or Indigenous health care worker) notes on their experiences with delivering the service to post-AMI/CS patients.Postimplementation interviews with TOC staff: Interviews undertaken with TOC service staff to determine their adoption of the service and willingness to deliver the service to patients.Implementation: Consistency, costs, and adaptations made during the delivery of the TOC service, both at the setting and individual levels.Communication outcome (discharge summary): Number of discharge summaries provided to primary care providers.Communication outcome (home visits): Number of follow-up home visit consultations provided within the TOC service.Process outcome (adaptations to the TOC service): Adaptations made to the TOC service by TOC staff during the study, as indicated through the delivery of activities in the TOC bundle and relevant notes during service delivery.Maintenance (and Sustainability): Long-term cost-effectiveness and local policy and procedure development.Economic sustainability: Sustainability of the intervention in the long-term based on the cost-effectiveness data.Local policy and procedures: Local policies and procedures have been developed during the pilot that will support long-term sustainable adoption of the TOC model.

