### RECARD Intervention: Pharmacist-Led TOC Service

Following patient consent, the TOC team will deliver assessments, activities, and medication reviews during the patient’s inpatient stay and for the 30 days postdischarge. The timeline for participant enrollment and assessments is shown in Table 1, created per the SPIRIT guidelines [23].

**Table 1. T1:** Participant timeline for enrollment and assessments during the trial period.

Time point	Enrollment	Intervention			Closeout
	During hospital admission	Discharge from hospital	Day 3 postdischarge	Day 14 postdischarge	Day 30 postdischarge
Enrollment					
Eligibility screen	✓				
Informed consent	✓				
Assessments					
Adherence assessment		✓		✓	
Pharmacist activities			✓	✓	
Nurse practitioner consult				✓	
Patient experience survey					✓

The RECARD activities will be described in an intervention bundle that is provided to support the decision-making capabilities of the TOC clinicians. Furthermore, this bundle is intended to empower TOC clinicians to make critical judgments when tailoring the TOC service to individual patients (eg, not repeating tasks that have been performed by ward pharmacists or not offering services that would be foreseeably ineffective).

The bundle will be developed based on previous work by the research team, including findings from a scoping review [1], local studies exploring TOC at the participating sites [33], and qualitative studies with clinicians and patients as part of the larger RECARD program (HREC/2023/MNHB/104151 [25]).

The work conducted in phase 1 seeks to inform the development of this bundle (see phase 1) [1]. The TOC service will be tailored to patients based on an assessment and identification of their individual needs and delivered during the hospital admission and across care transitions (Figure 3).

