### Precohort (Retrospective Data Collection)

Data will be collected from Health Information Management System to identify patients who are readmitted within 30 to 90 days. Re-presentation data for the ED will require data collection from Cerner FirstNet, as *ICD-10* codes are not used at the ED sites of the participating hospital. Sociodemographic characteristics, such as age, sex, height, weight, and Aboriginal and/or Torres Strait Islander status; clinical characteristics, such as current medications, medication history, comorbidities, laboratory results (ie, full blood count, renal function tests, liver function tests, coagulation studies, lipid levels, etc), and the Charlson Comorbidity Index; and hospitalization characteristics, such as length of stay, presenting complaint, ward location, cost of admission, and any associated events (readmissions, hospital-acquired complications, or other), and treating team will be compiled using available electronic sources and digital health records. These data will be extracted using hospital reporting systems such as the Hospital Based Corporate Information System and the integrated electronic medical record.

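### The long-term cost-effectiveness objective rests on a cost-effectiveness ratio that stops at day 30, when the service ends, so it cannot separate prevented from postponed readmissions or capture later benefit

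*Protocol article*

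**What the plan says.** **Objective.** Under Secondary Objective, the Maintenance domain of RE-AIM is defined as "Long-term cost-effectiveness and local policy and procedure development". Its economic component is "Sustainability of the intervention in the long-term based on the cost-effectiveness data".

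**Economic method.** The Economic Evaluation section is the only description of how cost-effectiveness data arise. Cost-effectiveness "will be determined using data from the primary analysis". The cost side is the net cost of the service and "any difference in the cost of unplanned 30-day readmissions (primary outcome) compared with the usual care group". The effect side is: "Effectiveness will be measured as the incremental reduction in unplanned 30-day readmissions, and this will be used to determine the incremental cost-effectiveness ratio". The section expects sensitivity analyses, including on outcome measures, but their attributes and limits are to be set after the main economic result is known. It also allows a switch to cost-minimization or cost-consequence analysis.

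**Length of the service.** Under RECARD Intervention: Pharmacist-Led TOC Service, the team acts "during the patient’s inpatient stay and for the 30 days postdischarge".

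**Later data.** All-cause readmissions at 60 and 90 days are listed under Secondary Objective. Medication-related readmissions at 60 and 90 days have their own section and are identified by ICD-10-AM Y codes. For the precohort, hospital records will be used to "identify patients who are readmitted within 30 to 90 days". The Postcohort data collection section promises the same variables in both periods, including the costs of readmissions.

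**The concern.** The objective and the measure have different horizons. The objective speaks of the long term, but both parts of the ratio, costs and effect, close at day 30. That is also the day on which support is withdrawn, so the ratio contains no observation of what happens to patients without the service.

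Two things are then invisible to it. A readmission moved from day 25 to day 40 counts as avoided, and its cost is never entered. A readmission that would have occurred on day 40 but is prevented by better adherence or handover earns no credit. The first makes the service look cheaper per readmission avoided than it is, and the second makes it look dearer.

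The stake is the argument for funding and wider adoption, which the protocol intends to base on this ratio. The primary effectiveness comparison and its power are not affected.

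**Working it through.** **1. The plan's own figure.** The Sample Size section gives 7% against 4.9%, significance level .05, power 0.80 and 1990 per period, inflated to 2211 for 10% dropout and refusal. The two-proportion formula (two-sided, pooled variance, no continuity correction) gives 1991 per period, and power at 1990 is 0.7999. Inflation gives 1990 / 0.90 = 2211.1. The planning figures reproduce and can be used for scale.

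**2. Readmissions credited at day 30.** A = 2211 × 0.021 = 46.4. With about 775 patients given the service, that is 775 / 46.4 = 16.7 treated patients per readmission avoided.

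**3. Effect of what happens after day 30.** Let f be the net share of A that reappears as readmissions in days 31 to 90; f is negative if further readmissions are prevented. Let S be total service cost and c the cost of one readmission, taken as constant.

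- Net readmissions avoided by day 90: A × (1 − f)
- Gross service cost per readmission avoided: S / [A × (1 − f)], which is the day-30 value multiplied by 1 / (1 − f)
- Net-cost ratio: {S − c × A × (1 − f)} / {A × (1 − f)} = S / [A × (1 − f)] − c
- Break-even service cost per treated patient, as a fraction of c: A × (1 − f) / 775

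| Assumed f | Net avoided | Treated per avoided | Multiplier on gross service cost per avoided | Break-even, % of c |
|---|---|---|---|---|
| −25% (added benefit) | 58.0 | 13.4 | 0.80 | 7.5 |
| 0% | 46.4 | 16.7 | 1.00 | 6.0 |
| 25% | 34.8 | 22.3 | 1.33 | 4.5 |
| 50% | 23.2 | 33.4 | 2.00 | 3.0 |

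Every value of f is an assumption, because the documents give no rates for days 31 to 90 and no costs. The multiplier applies to gross service cost per readmission avoided. The planned ratio uses net cost, so it shifts by the same absolute amount but not by the same factor.

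The 2.1 points were planned for medication-related readmissions. The Economic Evaluation section refers to unplanned 30-day readmissions and labels them the primary outcome, whereas the Outcome Measures section defines the primary outcome as medication-related. The table therefore shows scale only, and that label should be settled in the same edit.

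**4. Does other text extend the horizon?** The sentence on costing for a single year fixes the financial year and currency of the costs; it does not lengthen the readmission window. The quarterly team interviews cover adaptations, enablers and barriers, and supply no cost-effectiveness data. The sensitivity analysis might vary the outcome measure, but no longer horizon is named.

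**5. Timing.** The postcohort admits until November 30, 2026. Adding 90 days for a same-day discharge gives February 28, 2027, and longer stays end later. The Results section plans analysis for January to March 2027.

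**The case against.** The strongest reply has four parts.

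- **The trial does look past day 30.** All-cause readmissions at 60 and 90 days are secondary outcomes, to be compared in the same way as the primary. A gain that vanished by day 90 would be visible in the same report. This stands, and it rules out the inference that the trial counts readmissions only to day 30. That limit applies to the economic evaluation alone. What remains is that the later readmissions enter neither the costs nor the ratio.
- **The direction is not fixed.** A reader might infer that a 30-day window can only flatter the service. The documents do not support that. Adherence support, handover to primary care and Home Medicines Review referral could act beyond day 30, and the Impact section of the Discussion anticipates reductions at 60 and 90 days. If benefit persists, the 30-day ratio understates value.
- **Long-term may describe the service rather than patient follow-up.** The Phase 2 section uses similar language for a model that can be funded and maintained. On that reading a 30-day ratio is a legitimate input to viability. This softens the contradiction, but the Maintenance definition names long-term cost-effectiveness itself, and a ratio closing when the service ends is a weak basis for it.
- **Ninety days is not long-term either.** This is true, and it is why the wording should change along with the horizon.

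A condensed article may also leave economic detail to a fuller plan. The effect measure, the cost window and the objective are, however, all stated here, and the mismatch is among those statements.

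**Conclusion.** The point holds as a mismatch between a stated objective and the analysis meant to answer it. As written, the economic evaluation cannot distinguish prevented from postponed readmissions and cannot register benefit after day 30. On the planning figures, an assumed net postponement of 0%, 25% or 50% would leave about 46, 35 or 23 readmissions avoided and multiply gross service cost per readmission avoided by 1.0, 1.33 or 2.0. An assumed 25% of added benefit would multiply it by 0.80. These shares are illustrative. Whether postponement or lasting benefit occurs is not known from the documents, and no claim of bias in one direction follows. The change is worth making because the needed data are already planned in both cohorts. It does not touch the primary outcome, the sample size or the main effectiveness inference.

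**What to change.** - Keep the day-30 ratio, and prespecify beside it a day-90 analysis in both cohorts: service cost plus all-cause readmission costs to day 90, and cost per all-cause readmission avoided by day 90.
- Use all-cause readmissions for this comparison. Day-30 medication-related events have pharmacist and expert-panel review, while those at 60 and 90 days rest on Y codes alone, so a medication-related ratio would change case definition between horizons. Report the all-cause ratio at day 30 as well, so that the two horizons compare like with like.
- Base the Maintenance and economic-sustainability statement on both horizons, and word it as covering 90 days in place of long-term.
- State in the Economic Evaluation section whether the day-30 effect is medication-related or all unplanned readmissions.
- Close the day-90 data only when every postcohort patient has 90 days from discharge, which is not before the end of February 2027.

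**Cost.** A wording change and a costed extract from data already planned. Background readmissions will widen the day-90 interval, and the economic result may come a few weeks later.

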### Trial Hypothesis

Compared with usual care, the implementation of the interdisciplinary pharmacist-led TOC intervention will result in a significant reduction in 30-day medication-related hospital readmissions, be positively received by patients, and be cost-effective.

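### The economic conclusion rests on an ICER, but the only inferential criterion stated is P<.05 on an unnamed quantity, which cannot show whether a cost per readmission avoided is acceptable

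*Protocol article*

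**What the plan says.** Under Trial Hypothesis, the Protocol article says that the service will reduce 30-day medication-related readmissions, "be positively received by patients, and be cost-effective". The Secondary Objective section defines the economic endpoint: "Economic evaluation to assess the cost per readmission avoided".

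The Economic Evaluation section sets out the method:

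- **Result:** "Effectiveness will be measured as the incremental reduction in unplanned 30-day readmissions, and this will be used to determine the incremental cost-effectiveness ratio".
- **Cost sources:** "Costs will be quantified using data from the trial, the local hospital business unit, and expert opinion". No unit cost, standard deviation or programme cost is given.
- **Inferential criterion:** P "values less than .05 will be considered statistically significant". The section does not say whether this refers to the cost difference, the readmission difference or the ratio.
- **Other handling of uncertainty:** "Sensitivity analysis will be conducted to assess the level of confidence in the conclusions of the economic evaluation". The items expected to vary are resource and hospitalization costs, programme income and savings, and outcome measures. The specific attributes are to be identified, and "their variation limits will be determined after the primary cost-effectiveness analysis has been completed".

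Separately, the Statistical Analysis section sets a 5% level with 95% confidence intervals for the primary and secondary outcomes and names multivariable logistic regression as the method.

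**The concern.** An ICER is a ratio of two uncertain and correlated differences. Whether it is acceptable depends on what the payer would give to avoid one readmission. A test of zero cost difference, or of zero effect, does not contain that value, so neither result answers the question in the hypothesis.

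The planned sensitivity analysis does not fill the gap as described. Moving unit costs and other inputs up and down shows how the ICER depends on those inputs. It does not show how far incremental cost and effect would move together in another sample of patients. Setting the limits after the result is known weakens it further as a check on confidence.

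Cost-effectiveness is one of three parts of the trial hypothesis, and the Secondary Objective section bases economic sustainability on the same data. If the P value came to be read as the economic test, a service that prevents readmissions and saves money could be reported as showing no significant difference. The ICER would then carry no statement of how likely it is to be favourable.

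**Working it through.** **Step 1. Reproduce the plan's own figure.** The Sample Size section gives 7% versus 4.9%, significance level .05, power 0.80, 1990 per period and 2211 after 10% dropout. A two-sided comparison of two proportions without continuity correction gives 1991 (pooled variance) or 1989 (unpooled). Power at 1990 is 0.800, and 1990/0.90 = 2211.1. The stated size reproduces, and it is a size for the readmission rate.

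**Step 2. What decides acceptability.** Let ΔE be readmissions avoided per patient, ΔC the incremental cost per patient and λ the value placed on one readmission avoided. The service is acceptable if λΔE − ΔC > 0. The variance of that quantity is λ²Var(ΔE) + Var(ΔC) − 2λCov(ΔE, ΔC). Tests of ΔC = 0 or ΔE = 0 involve neither λ nor the covariance.

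**Step 3. Power if P<.05 were applied to cost.** Express cost in units of C, the mean cost of a readmission. CV is the coefficient of variation of cost per readmission. k is programme cost as a share of the gross saving on readmissions. Both are assumptions, because the document gives no costs.

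- Variance per patient in each period: p(1 + CV²) − p², plus a negligible term for the 35% who receive the service.
- Net saving per patient: 0.021(1 − k).
- Break-even programme cost (k = 1): 0.021/0.35 = 0.06C per treated patient.

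Worked case, CV 1 and k = 0, n = 1990:

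- Pre: 0.07 × 2 − 0.07² = 0.1351.
- Post: 0.049 × 2 − 0.049² = 0.0956.
- Standard error: √(0.2307/1990) = 0.01077.
- z = 0.021/0.01077 = 1.95, so power is about 50%.

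Power with 1990 per period:

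| CV | k = 0 (free) | k = 0.25 | k = 0.5 |
|---|---|---|---|
| 0 | 80% | 56% | 29% |
| 0.5 | 70% | 46% | 24% |
| 1 | 50% | 31% | 16% |
| 1.5 | 33% | 21% | 12% |
| 2 | 23% | 15% | 9% |

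With 2211 per period the free-service column becomes 84%, 75%, 54%, 36% and 25%. At n = 1990, power falls to 50% or less once k reaches about 0.30 at CV 0 or about 0.21 at CV 0.5. At CV 1 or more it is already there at k = 0.

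**Step 4. How the P value and the estimate can diverge.** At CV 1 and n = 1990, the chance that the point estimate shows a saving is 97%, 93% and 84% for k = 0, 0.25 and 0.5, against power of 50%, 31% and 16%. With k = 0.5, the chance that estimated net benefit is positive rises from 84% at λ = 0 to 94% at λ = 0.5C and 97% at λ = C. The answer moves with λ, and a single P value on cost cannot show that.

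**Step 5. If all unplanned readmissions are costed.** At an assumed 15% base rate, the same 2.1-point fall and CV 1, power is 26%, 16% and 10% for k = 0, 0.25 and 0.5.

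The normal approximation ignores skewness, and the model leaves out costs other than readmission and programme. Adding other cost variance would lower power further.

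**The case against.** **No decision rule is stated.** A reader might infer that the protocol will declare or reject cost-effectiveness on P<.05. The text does not say so: it labels small P values significant and names no tested quantity. The ICER would be reported whatever the P value. This stands.

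**The P value may refer to the readmission difference.** Power would then be the planned 80%. This reading is possible, but the Statistical Analysis section already sets the 5% level for the outcomes. On this reading the sentence is redundant, and the economic result has no stated criterion for sampling error.

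**The result need not usually be non-significant.** A reader might infer that a cost-saving service would usually fail the test. That depends on costs the document does not give. It is untrue for a cheap programme with a CV of about 0.5 or less, and at 2211 per period a free service with CV 1 reaches 54%.

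**Other uncertainty handling is planned.** Sensitivity analysis is intended to address confidence, and the text does not settle whether it is deterministic or probabilistic. Cost-effectiveness is also listed among the secondary outcomes, which are to have 95% confidence intervals. The first objection has some force, although input variation within limits points to a deterministic analysis. The second has little, because the named logistic model does not suit cost or a ratio.

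**Details may sit elsewhere.** A threshold or bootstrap may be specified in a fuller economic plan, so their absence from a journal article is no error in itself. The point concerns the criterion that is printed.

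**Conclusion.** The concern holds in limited form. The section makes an ICER its result and states one inferential criterion, attached to nothing, that cannot judge an ICER. As described, nothing carries the joint sampling error of cost and effect into the cost-effectiveness conclusion, and the sensitivity limits are set after the result is known.

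The size is conditional. If P<.05 were applied to the cost difference under exactly the planned effect, power would run from 80% (no variation in cost per readmission, free service) to 9% (CV 2, programme cost half the gross saving), with 1990 per period. CV and programme cost are assumptions throughout. The supported statement is that a cost-saving service could readily be labelled not significant. The documents do not support saying that it usually would be, or that the protocol makes P<.05 the test of cost-effectiveness.

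Severity is minor: the primary analysis and sample size are unaffected.

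**What to change.** In the Economic Evaluation section, replace the P<.05 sentence with estimation:

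- Report incremental cost and incremental readmissions avoided per patient, with the ICER.
- Obtain joint uncertainty from a bootstrap that resamples each patient's cost and outcome together, within hospital and period.
- Show the result as a cost-effectiveness plane and an acceptability curve over a range of values per readmission avoided fixed before analysis. State the conclusion as a probability over that range.
- Fix the sensitivity-analysis attributes and limits before the economic result is seen.

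The cost is some wording and modest programming on data already being collected. The Results section plans analysis for January to March 2027 and reports no preliminary analysis, so the change can still be prespecified. The small downside is that the headline becomes a probability, not a yes/no significance statement.

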### Sample Size

It is expected that, under conditions of usual care, the rate of medication-related hospital readmissions within 30 days among patients discharged following an AMI is 7% [40]. Interventions have reduced this rate from 7% to 4.9% (an absolute risk reduction of 2.1%) [41]. As mentioned previously, only a subset of the population (those identified as being at highest-risk based on model scoring and/or clinician referral) will be targeted to receive the intervention. Guided by previous studies and resources, we expect to prioritize the top 25% of patients at high-risk of medication-related readmission [42]. An additional 10% of patients are expected to be referred by the treating team. However, the final proportion of patients who will be triaged for intervention will be guided by a local audit following the development of the risk model. Because the high-risk patients will likely have a higher rate of potential readmission (ie, >7%), we expect that an intervention applied to only this group will still produce an absolute risk reduction of at least 2.1% averaged across the entire intervention sample, even though we expect the risk in the low-risk group to remain unchanged. Therefore, the sample size calculation is based on the overall sample required, not just the high-risk group.

Assuming a baseline risk of readmission of 7% and a significance level of .05, a sample size of 1990 participants is required in both the prestudy and intervention periods (ie, a total of 3980 patients across both prestudy and intervention periods) to detect an absolute risk difference of 2.1% with a power of 0.80. We assume a minimal dropout and refusal rate of 10%; taking this into account, we aim to recruit 2211 participants into each 12-month period (a total of 4422 participants across both the prestudy and intervention periods). We expect 35% of patients (~775 patients) to be flagged as high risk, consent to the study, and be given the TOC intervention. The remainder of the patients enrolled in the study will be given usual care as described earlier. Delivering the TOC service to 775 participants across the study sites over 12 months is both logistically feasible and achievable.

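### Economic sensitivity analysis: attributes and limits are to be set after the cost-effectiveness result is known, with no prior rule for choosing them

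*Protocol article*

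**What the plan says.** The Economic Evaluation section gives the purpose of the sensitivity analysis: "Sensitivity analysis will be conducted to assess the level of confidence in the conclusions of the economic evaluation". On content it says: "Sensitivity analysis is expected to include variations in resource costs, hospitalization costs, remuneration and savings from the program, and outcome measures". The same sentence then sets the order of work: "specific attributes will be identified and their variation limits will be determined after the primary cost-effectiveness analysis has been completed".

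The quantity at issue is the incremental cost-effectiveness ratio (ICER). "Effectiveness will be measured as the incremental reduction in unplanned 30-day readmissions, and this will be used to determine the incremental cost-effectiveness ratio". The section also allows the form of the evaluation to change: "The analysis method may be adapted to a cost-minimization analysis or cost-consequence analysis, if required, once the primary outcomes have been analyzed".

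Cost-effectiveness is part of the Trial Hypothesis, under which the service will "be positively received by patients, and be cost-effective". It is also listed as an outcome under the Secondary Objective, where it feeds the economic sustainability outcome. No other section of the article fixes the attributes or their limits earlier.

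**The concern.** A sensitivity analysis of this kind asks whether plausible variation in the inputs would change the conclusion. Once the base-case result is known, so is the distance to the point at which the conclusion changes. Limits chosen at that stage can fall short of that point or beyond it, and the report alone would not show why they were chosen.

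This is not detail that a condensed article leaves to a fuller plan. The article states the sequence outright: result first, limits second. An economic analysis plan that fixed the limits beforehand would contradict it.

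At stake is how far a reader can trust a statement that the cost-effectiveness finding is robust. That finding is meant to inform wider implementation of the service. The permission to change the form of the evaluation after the primary outcomes are analyzed is a separate matter, but it means that the limits would not be the only choice made after results are known.

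**Working it through.** The sensitivity analysis has no stated figure to reproduce. The check uses the Sample Size section, which supplies the planned effect behind the ICER.

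**Inputs (Sample Size section)**
- Usual-care rate 7% and significance level .05 ("Assuming a baseline risk of readmission of 7% and a significance level of .05"); rate with the intervention 4.9%; absolute reduction 2.1 points; power 0.80.
- 1990 patients per period.
- 35% of the post-period cohort expected to receive the service.

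**Step 1: reproduce the plan's figure.** For two proportions, two-sided, with pooled variance under the null and no continuity correction:

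n = [1.96·√(2 × 0.0595 × 0.9405) + 0.8416·√(0.07 × 0.93 + 0.049 × 0.951)]² / 0.021² = 1991

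The plan states 1990. Unpooled variance gives 1989. The planning values are consistent with each other and can be used.

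**Step 2: patients treated per readmission avoided at the planned effect.** 0.35/0.021 = 16.7.

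**Step 3: how this enters the ICER.** Let c be the service cost per treated patient and r the cost of one readmission; the document gives neither. The incremental cost per cohort patient is 0.35c − ARR × r, where ARR is the absolute risk reduction. Dividing by ARR:

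ICER = (0.35/ARR)c − r

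With c and r held constant, any spread in 0.35/ARR passes straight into the cost per readmission avoided, in multiples of c.

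**Step 4: statistical uncertainty of the effect at the planned size.**
- SE = √(0.07 × 0.93/1990 + 0.049 × 0.951/1990) = 0.0075.
- 95% interval: 2.1 ± 1.96 × 0.75 = 2.1 ± 1.47, or 0.63 to 3.57 points.
- Patients treated per readmission avoided: 0.35/0.0357 = 9.8, and 0.35/0.0063 = 55.6 (55.4 with the unrounded bound).

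**Step 5: an illustrative fixed-percentage limit.** The ±20% is an assumption; the protocol proposes no figure.
- 2.1 × 0.8 = 1.68 points, so 0.35/0.0168 = 20.8.
- 2.1 × 1.2 = 2.52 points, so 0.35/0.0252 = 13.9.
- The half-width is 0.42 points, against 1.47 for the confidence interval: 0.42/1.47 = 29%.

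| Limit on the effect | Effect (points) | Treated per readmission avoided |
|---|---|---|
| Planned value | 2.1 | 16.7 |
| ±20% (illustrative) | 1.68 to 2.52 | 20.8 to 13.9 |
| Expected 95% interval | 0.63 to 3.57 | about 55 to 9.8 |

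The ICER range from the effect alone is 20.8 − 13.9 = 6.9c under the first limit and 55.4 − 9.8 = 45.6c under the second. Either could be reported as a sensitivity analysis under the current wording.

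**The case against.** The strongest reply is that the plan is not empty. The domains are named in advance. The Statistical Analysis section promises 95% confidence intervals for the primary outcome, so a reader could carry the effect's uncertainty into the ICER whatever limits the team chose. Limits set later may be chosen in good faith, and limits taken from data can have numerical values only after the data are analyzed.

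Much of this stands, and it rules out several stronger readings.

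- A reader might infer that the sensitivity analysis cannot measure confidence at all. The named domains and the promised interval do not support that. The defect is the lack of a prior rule. The named domains are only expected, and the promised interval does not cover the cost inputs.
- A reader might infer that narrow limits would guarantee a finding of cost saving. That fails once two inputs move together. If a readmission cost 20 times one service episode (an assumption), raising service cost by 10% and lowering readmission cost by 10% gives 20 × 0.9/1.1 = 16.4, below the break-even of 16.7. Cost-neutrality is also not the stated outcome, which is cost per readmission avoided; a service can be cost-effective without saving money.
- A reader might take the sentence that P "values less than .05 will be considered statistically significant" as a test of the ICER. The section does not say so, and a P value can apply to the difference in readmission cost that the same paragraph describes.

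What the reply does not do is justify the stated order. Although numerical limits may have to wait for data, the rule that produces them need not.

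**Conclusion.** The point holds in a limited form. The article commits to choosing sensitivity attributes and limits after the cost-effectiveness result, with nothing to constrain the choice, so a claim of robustness could not be told apart from a convenient choice of limits. It affects the economic objective only; the primary clinical comparison and the base-case ICER are untouched.

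On size, the effect's own expected uncertainty spreads patients treated per readmission avoided from about 9.8 to 55 around a planned 16.7, while a ±20% limit would show 13.9 to 20.8. This rests on the planned 2.1-point effect being observed, 35% being treated, 1990 analyzed per period, an unadjusted comparison, and the ICER using the reduction in medication-related readmissions for which the sample size was set. The Economic Evaluation section refers to unplanned readmissions but labels them the primary outcome. The ±20% is illustrative. The article gives no unit costs or decision threshold, so whether the final conclusion would change cannot be calculated from it.

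**What to change.** Replace the sentence so that the attributes, and the rule for deriving each limit, are fixed before the cost-effectiveness result is seen. For example:

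- effect: the 95% confidence interval from the primary model, with a stated method for turning the logistic regression result into an absolute reduction;
- readmission cost and service time: a prespecified interquartile or bootstrap range;
- unit costs: one common percentage, stated in advance.

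Any attribute or limit added later stays permissible but is labeled post hoc.

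The cost is a short paragraph in the economic analysis plan and slightly less flexibility; no new data are needed. There is time: the Results section reports that no preliminary analysis has been undertaken and plans the analysis for January to March 2027. Admission cost is already among the data items for the retrospective cohort, so the rule for hospitalization cost can be drafted without the post-period result.
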